#### Interim analyses {21b}

Not applicable.

#### Methods for additional analyses (e.g. subgroup analyses) {20b}

Interobserver agreement for cineradiographies and 4D CT between two radiologists will be evaluated using the kappa statistic.

#### Methods in analysis to handle protocol non-adherence and any statistical methods to handle missing data {20c}

One exclusion criterium for the historical cohort will be missing data. The comparative historical cohort will consist of 80 patients to account for a probably greater extent of heterogeneity in the retrospective data.

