### Eligibility criteria {10}

Eligible patients for prospective inclusion with suspected SLL tear are scheduled for diagnostic arthroscopy. 40 consecutive patients will be enrolled according to predefined criteria:
Inclusion criteria: patients > 18 years, written consent.Exclusion criteria: inability to consent, patients < 18 years, pregnancy, considerably limited range of radio-ulnar motion, incompliance to the rehearsed radio-ulnar motion, scapholunate advanced collapse (SLAC), previous carpal instability or carpal operation, incomplete historical records.
Patients with distal radius fractures and previous stabilization of the fracture will not be excluded per se. Only if these patients are not able to perform the required radio-ulnar motion due to pain or stiffness, they will be excluded. Patients with previous carpal instabilities or carpal operations i.e. due to scaphoid fractures will be excluded from this study as well.

A historical cohort consisting of 80 consecutive patients with the same inclusion and exclusion criteria who were diagnosed with cineradiography preoperatively during the pre-4D CT era will serve as comparison for the diagnostic value of the new method.

Two radiologists with more than 6 years of experience in musculoskeletal radiology will evaluate preoperative 4D CT scans and cineradiographies independently.

Arthroscopies will be performed by specialized hand and wrist surgeons.

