#### Intervention description {11a}

All patients with a typical trauma mechanism and wrist pain presenting through the ambulance or emergency room will be screened for eligibility. Patients will be examined and will receive radiographs of the wrist in two planes routinely. In cases of suspected SLL tear and indication for arthroscopy, patients will be informed about the possibility of study participation by the attending hand surgeon.

According to the inclusion and exclusion criteria 40 participants will be enrolled consecutively after written consent.

4D CT scans of the injured wrist will be performed preoperatively and analyzed by two specialized radiologists. Coronal reconstructions will be used to measure the maximum and minimum scapholunate distance (SLD). On sagittal reconstructions the scapholunate (SL) and radiolunate (RL) angle will be determined to classify SLL tears as stable or unstable.

The patients will not be exposed to radiation for research purposes. Arthroscopy will be performed as the diagnostic gold standard within the same week to classify the type of SLL tear according to the European Wrist Arthroscopy Society (EWAS) and Geissler [16, 17]. Primary reconstruction and temporary arthrodesis will be performed when necessary, but the surgical therapy will not be part of the study.

We will conduct an additional screening of historical patient records for eligibility, inclusion, and exclusion criteria. These historical patients with a typical trauma and wrist pain were also examined clinically and received radiographs of the wrist in two planes routinely. In cases of suspected SLL tear, cineradiography was performed before arthroscopy. After written consent 80 consecutive patient who were diagnosed through cineradiography before arthroscopy will be enrolled. Measurement of minimum and maximum SLD on anterior-posterior projections, of SL angle, and RL angle on lateral projections will be measured to classify SLL tears as stable or unstable and to compare these results to the findings of arthroscopy. The diagnostic accuracy of cineradiography will serve as a comparison for the sensitivity and specificity of 4D CT in suspected SLL tears.

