#### Criteria for discontinuing or modifying allocated interventions {11b}

Eligible patients who are incapable of performing the radio-ulnar motion required for dynamic evaluation of the SLL will be excluded from the study. Patients who withdraw their consent for arthroscopy will be excluded from the study.

Patients will be able to withdraw their consent for participation at any time during the trial. Patients with incomplete historical records will be excluded from retrospective analysis.

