#### Sample size {14}

The study will be conducted and analyzed in an exploratory fashion. Therefore, formal sample size calculations are deferred by the investigators. Instead, yearly patient numbers were estimated, and the number of participants was adapted to a two-year study design which results in a recruiting target of 40 patients used for estimation of diagnostic accuracy of 4D CT. The comparative historical cohort used for estimation of diagnostic accuracy of cineradiography should consist of 80 patients to account for a probably greater extent of heterogeneity in the retrospective data due to the fact that these were collected by different clinicians who were not instructed on data collection specifically for this trial.

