#### Recruitment {15}

Previously, approximately 30 arthroscopies have been performed at the study center for suspected SLL tears each year. Thus, enrolment of 40 patients in 2 years seems reasonable. To assure maximum screening and identification of eligible patients, all hand surgeons at the center will be involved in the process. Radiologists are sensitized to communicate radiographs with abnormalities of the SL joint to increase the screening cohort.

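### Excluding historical patients for missing data, whatever is missing, makes the cineradiography comparator a complete-case sample and may bias its contrast with 4D CT in an unknown direction

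*Protocol article*

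**What the plan says.** The rule on missing historical data appears in three places of the protocol article.

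- Section {20c}, on missing data: "One exclusion criterium for the historical cohort will be missing data".
- Section {11b}, on discontinuation: "Patients with incomplete historical records will be excluded from retrospective analysis".
- Section {10}, on eligibility, lists incomplete historical records among the exclusion criteria.

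None of these says which items must be present, or treats the reference standard and the index test differently.

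On how the cohort is formed, section {10} describes "A historical cohort consisting of 80 consecutive patients with the same inclusion and exclusion criteria". Section {11a} states "We will conduct an additional screening of historical patient records for eligibility, inclusion, and exclusion criteria" and then "After written consent 80 consecutive patient who were diagnosed through cineradiography before arthroscopy will be enrolled". Section {20c} adds "The comparative historical cohort will consist of 80 patients to account for a probably greater extent of heterogeneity in the retrospective data".

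The cohort supplies one side of the second primary objective in section {7}, the comparison of the two methods' diagnostic accuracy. In the 4D CT arm, sections {10} and {11b} remove patients who cannot perform the radio-ulnar motion or do not comply with it. The Discussion undertakes to report how many patients dropped out or were excluded, and why.

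**The concern.** A historical record can be incomplete in two quite different ways. If the arthroscopic stage is absent, the patient cannot enter a sensitivity or specificity calculation, and exclusion is unavoidable. If the stage is known but a scapholunate distance or carpal angle is missing or cannot be evaluated, the true status is known and only the index test has failed to deliver. Excluding that patient removes the failure from the record of the test. As written, the rule treats both cases alike.

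The sample size section ({14}) concedes that the historical data were collected by clinicians who had no instructions for this trial, so gaps are plausible. If the chance of a gap is related to whether cineradiography would have been right or wrong, sensitivity and specificity in the retained patients differ from those in all eligible patients, and the contrast with 4D CT shifts with them. The larger cohort that {20c} offers does not help here: more patients narrow the interval around the estimate but do not remove selection.

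Later analysis may not be able to repair this. Section {11a} applies the criteria when records are screened, and section {5d} has the data of the 80 files passed to the statistician. Nothing says that excluded records travel with them.

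**Working it through.** **1. Is there a figure to reproduce?** No. The size of 80 is a judgement: section {14} says "Therefore, formal sample size calculations are deferred by the investigators". No missing rate, prevalence or expected accuracy is given. Every rate below is my assumption.

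**2. What does 80 count?** The text allows two readings.

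- *After exclusion.* Incompleteness is an eligibility criterion, screening precedes enrolment, and the cohort consists of 80. With missing share d, the otherwise eligible records needed are 80/(1 − d): 89, 100, 115 and 134 for d = 10%, 20%, 30% and 40%. Section {15} says "Previously, approximately 30 arthroscopies have been performed at the study center for suspected SLL tears each year". At 30 a year, these take about 3.0, 3.3, 3.8 and 4.4 years of records, against 80/30 = 2.7 years with nothing missing.
- *Before exclusion.* Section {11b} excludes from the analysis, not from enrolment. Then 80 × (1 − d) = 72, 64, 56 or 48 patients remain.

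On either reading the analysed patients are complete cases. On the first, a series filtered on completeness is not strictly consecutive.

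**3. Which way could the bias go?** Let S be sensitivity in all eligible unstable wrists, cTP the share of true-positive records that are complete, and cFN the share of false-negative records that are complete. Then

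complete-case sensitivity = S·cTP / [S·cTP + (1 − S)·cFN].

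With S = 0.80 assumed:

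| cTP | cFN | Calculation | Complete-case sensitivity |
|---|---|---|---|
| 0.8 | 0.8 | 0.64/(0.64 + 0.16) | 0.800 |
| 0.9 | 0.7 | 0.72/(0.72 + 0.14) | 0.837 |
| 0.9 | 0.5 | 0.72/(0.72 + 0.10) | 0.878 |
| 0.7 | 0.9 | 0.56/(0.56 + 0.18) | 0.757 |
| 0.5 | 0.9 | 0.40/(0.40 + 0.18) | 0.690 |

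If completeness depends only on true stability, cTP = cFN and there is no bias. If missed tears are the less complete records, cineradiography is flattered; if they are the more complete ones, it is penalised. Specificity behaves in the same way, with true negatives and false positives. Nothing in the documents selects a row.

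**4. How large could it be?** Let S now be the complete-case sensitivity and m the share of unstable wrists dropped although their stage is known. Full-group sensitivity lies between S(1− m), if all dropped patients would have been missed, and S(1 − m) + m, if all would have been detected. With S = 0.80:

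| m | Lower | Upper |
|---|---|---|
| 10% | 0.72 | 0.82 |
| 20% | 0.64 | 0.84 |
| 30% | 0.56 | 0.86 |

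In counts for m = 20%: 32 of 40 retained wrists detected and 10 dropped gives 32/50 = 64% to 42/50 = 84%. The exact 95% interval for 32/40 is 64.4% to 90.9%. A loss of that size would thus leave a range of 20 percentage points, against 26.5 points for sampling error, and the confidence intervals planned in {20a} do not reflect it.

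**5. Is the other arm unfiltered?** No. Section {10} excludes limited motion and non-compliance with the rehearsed movement. Section {11b} removes patients incapable of the movement under a discontinuation heading, so possibly after enrolment. An important source of non-evaluable 4D CT scans may leave the data in this way.

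**The case against.** The strongest reply is that the rule may be harmless. The required items are not listed, so an incomplete record could simply be one without a surgical report or without images. Section {10} has two radiologists evaluate the cineradiographies, {11a} says distances and angles will be measured for historical patients, and {20b} plans interobserver agreement for both methods. That points to fresh measurement from stored images, in which case a value absent from an old report need not make a patient incomplete. This stands in part: it shows that most of the remedy fits existing work. It does not settle the matter, because Table 3 in {13} names inspection of cineradiography reports as the historical step, and no section limits the exclusion to a missing reference standard.

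The study is also declared exploratory, with no margin or test for a bias to overturn, and exclusions will be reported with reasons. Both are true and limit the consequence. But bias in a reported estimate does not depend on a hypothesis test, and a count of exclusions does not change the estimate. A not-evaluable category and bounding analyses could sit in an analysis plan that is not shown, so their absence is no fault. The point is the stated exclusion rule.

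Three stronger readings are tempting and not supported.

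- A reader might infer that dropped patients are replaced until 80 complete records are reached. No section mentions replacement, and {11b} leaves open that fewer than 80 are analysed.
- A reader might infer that the bias works against 4D CT, on the ground that hard or equivocal cineradiograms go missing. The documents do not say that such studies are excluded, and steps 3 and 4 allow either sign or none.
- A reader might infer that only the historical arm is filtered. Step 5 shows otherwise, and the motion exclusions could flatter 4D CT.

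**Conclusion.** The concern holds in this form: the protocol excludes historical patients for missing data without separating a missing arthroscopic stage from a missing or non-evaluable index measurement. Cineradiography accuracy is therefore a complete-case estimate, and a primary comparison may be biased by an amount and in a direction that the documents do not fix. The figures are illustrations. With an assumed complete-case sensitivity of 80%, assumed losses of 10% to 30% of unstable wrists give full-group ranges from 72–82% to 56–86%; with no such losses the problem vanishes. Whether 80 is counted before or after exclusion also needs to be stated. The change should be made, and while the excluded records can still be identified, but it does not invalidate the study.

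**What to change.** - Limit the missing-data exclusion in {10}, {11b} and {20c} to historical records without a usable arthroscopic stage.
- Where the stage is known, keep the patient and measure the scapholunate distances and the scapholunate and radiolunate angles from the stored cineradiogram. If that fails, record the index test as *not evaluable*.
- Use the same category for 4D CT patients whose scan was attempted but could not be evaluated. Table 6 then needs a third option beside stable and unstable.
- Report sensitivity and specificity for both methods on evaluable patients, and again with all non-evaluable results counted as wrong and then as right.
- State whether 80 is the number before or after exclusion.

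The cost is amended wording in three sections and one form, some re-measurement by radiologists who already read these studies, and one sensitivity analysis. No new patients are needed. The downside is that accuracy figures may come out less favourable, or with a wider range, for either method.

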#### Plans to give access to the full protocol, participant level-data and statistical code {31c}

The full protocol, anonymized participant level-data, and statistical code can be provided upon request.

### Oversight and monitoring

#### Composition of the coordinating center and trial steering committee {5d}

This single center, investigator-initiated study will not be monitored independently. Each department will be responsible for the integrity of the data. One physician of each department is selected for data management and digitalization. After discharge of all 40 participants and protocolling of the data of all 80 patient files the responsible hand surgeon and radiologist will transfer pseudonymized separate data sets to the statistician. The statistician will receive both data sets and will be the only one with access to the final data set.

#### Composition of the data monitoring committee, its role and reporting structure {21a}

The data monitoring committee will consist of one radiologist, one hand surgeon, and the statistician of the study center. After data acquisition will be complete, integrity of digital data will be cross-checked by hand surgeons and radiologist using the paper CRFs. The statistician will be the only member with insight to the finalized combined dataset. There will be no external monitor.

#### Adverse event reporting and harms {22}

The threshold for acute stochastic skin damage has been reported to lie around 2 Gy [25] and thus almost 60x higher than the skin doses of reports about 4D CT of the wrist in-vivo and in-vitro [12, 26]. Nevertheless, concerns about deterministic cells damages by low-dose examinations arise recurrently. Radiation exposure is measured during 4D CT and checked for compliance with local regulations (https://www.bfs.de). Violations have to be reported (https://www.aerztekammer-berlin.de/10arzt/39_Aerztliche_Stelle/05_AESQSB_kurz_dargestellt/index.html).

#### Frequency and plans for auditing trial conduct {23}

Audits will not be part of this trial.

#### Plans for communicating important protocol amendments to relevant parties (e.g. trial participants, ethical committees) {25}

Amendments to the study protocol will be reported to the ethics board at the University Medicine Greifswald, Germany (http://www2.medizin.uni-greifswald.de/ethik/). Amendments cannot affect the standard of care; therefore, participants won’t be informed about changes. The investigators will meet once every 3 months to discuss protocol relevant issues.

#### Dissemination plans {31a}

This study will be published open-access in a peer-reviewed journal independent of the results. Prior to publication, results will be available on a preprint server for transparency of any modifications of the manuscript.

## Discussion

Studies of diagnostic accuracy have the potential to improve the standard of medical care. Well conducted studies which are reported adhering to standardized guidelines allow for a generalizability of the topic [15]. Observational studies have the advantage of answering certain scientific questions in a rather descriptive manner while excluding any harm induced by study specific interventions. The lack of direct comparisons through a strict randomization protocol is a disadvantage of this study type.

On these grounds it can be expected that this prospective observational study will result in reliable calculations of diagnostic parameters of 4D CT of the wrist in diagnosing instable SLL tears. The comparison with a historical cohort on the other hand, will always be a means to atone for missing randomization and prospective comparisons.

In order not to over-estimate the clinical relevance of 4D CT, it will be crucial to minimize drop-outs after conducting the index test. The study protocol requires that all patients will have to have an indication for the reference test arthroscopy first to be eligible as participants. The number and reasons for drop-outs and excluded patients will be described in detail in the study report.

It can be expected that a positive outcome of the study and an increasing availability of 4D CT could have a grave impact on out-patient care. Since approximately 5% of all wrist sprains have an associated injury of the SLL [27], a broad availability of reliable primary imaging might improve early detection rates, reduce the incidence of resulting osteoarthritis, and the number of unnecessary diagnostic arthroscopies in the future.

### Trial status

Protocol Version 1.0. Recruitment of first participant: 06/16/2020. Recruitment will be completed 06/2022.

## Data Availability

The final anonymized trial dataset can be supplied upon personal request. Detailed statistical analysis will be included in the published article as supplementary information files.

## Abbreviations

CT: Computed tomography
MRI: Magnetic resonance imaging
SLL: Scapholunate ligament
SLAC: Scapholunate advanced collapse
SLD: Scapholunate distance
SL: Scapholunate
RL: Radiolunate
CRF: Case report form
EWAS: European Wrist Arthroscopy Society
TLD: Thermoluminescence dosimeter
AUCs: Areas under the curve
DLP: Dose length product
CTDI: CT dose index
AUROC: Area under the receiver operating characteristic
STARD: Standards for Reporting of Diagnostic Accuracy Studies
MCU: Midcarpal ulnar
MCR: Midcarpal radial
